### Sampling and data collection

To collect valuable qualitative data during Phase 1 of the study, purposive sampling (non-probability sampling) will be utilized. During the quantitative Phase 2, random sampling will be utilized to create an unbiased representation of the study population. The random allocation will be generated by MD. ZK, EL and the research assistants will be responsible for enrolling and assigning participants.

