### Study site

The study sites are two high volume community health centers (CHC) in the Tshwane district of Gauteng province in South Africa, FF Ribeiro Clinic and Kgabo CHC. FF Ribeiro Clinic is situated in the central business district of Tshwane, catering to an urban community and Kgabo CHC, is situated in a large settlement, Ga-Rankuwa, catering to a semi-rural community.

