#### Phase 2 sampling & data collection

During Phase 2 of the study, the randomized control trial, researchers and research assistants will randomly recruit women attending an antenatal care visit and their partners, inviting them to participate in the randomized control trial. Every participant will be required to provide informed consent before they can be included in the sample. Participants will be randomized into either the intervention group or the control group until the sample size of 420 has been reached. To implement the randomization, a table with the generated randomization sequence will be used, and as a participant agrees to participate in the study, they will be sequentially allocated to a row in the table that will determining the group that the participant will form part of. The sample size for the randomized control trial, was determined using the primary outcome of the study, change in knowledge. We will allocate participants equally to the treatment and control groups, through a balanced computer-generated random sequence. We use a 0.05 level of significance (*P* < 0.05) and a power of 0.9 with a two tailed test for significance.

Our hypothesis is that at the 3-month follow-up, participants in the control group will score 43% on the intention to change behavior score (12 points out of 28 points in the survey). We propose that after the 3-month follow-up the intervention group will score 61% (17 out of 28 points). This is an 18% absolute increase and a 1.41 times relative increase. A sample size of *n* = 140 was calculated for the intervention group and the control group. We then used an increase of 50% to account for potential participant drop-outs, bringing the sample size for the intervention group to *n* = 210 and the sample size for the control group to n = 210, spread equally and randomly across the two sites (Kgabo CHC[urban site] and Ga-Rankuwa[rural site]). Thus, a total of *n* = 420 participants for the entire randomized control trial will be required. These sample size calculations were carried out on G-Power 3.1.9.6.

Sample size calculations were based on the difference between two independent proportions using a z-test (Power: 0.9, Alpha 0.05, Allocation N1/N2: 1, p1 = 0.43, p2 = 0.61). The sample size per group was rounded up to the nearest 10 patients (N1 = 140, N2 = 140).

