Expectant mothers assigned to the intervention group will watch the 10 Amandla Mama videos and their partners will receive the same 10 Amandla Mama videos via the social media platform, WhatsApp or short messaging service (SMS). The expectant mothers will be asked to provide the researchers with their contact details and the contact details of their partners. Partners who agree to participate in the study and who provide informed consent will receive the Amandla Mama videos by SMS or WhatsApp. The control group will receive existing treatment as usual-antenatal care only.

After 3 months, knowledge, behavioral intent, and user satisfaction surveys will be administered telephonically to all participants. The follow-up is conducted after 3 months to test long-term retention providing a better predictor for ongoing change. The research assistants under supervision of the researchers, will administer the telephonic survey. Data collected from participants who discontinue with or deviate from the study will not be used.

Surveys for the expectant mothers consist of a total of 61 questions: 10 background questions, 15 behavioral intention questions, 30 knowledge questions and 8 user satisfaction questions (refer to Additional file 1: Annexure 2). Surveys for partners consist of a total of 63 questions: 8 background questions, 18 behavioral intention questions, 30 knowledge questions and 8 user satisfaction questions (refer to Additional file 1: Annexure 3). The user-satisfaction questions, which consider how satisfied the participants are with the Amandla Mama videos, will only be administered to participants in the intervention group. All Phase 2 study participants will receive ZAR 100 to compensate them their time and expenses incurred by participating in our study.

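### The staff who enrol also assign from a sequence table with no described concealment, the same role collects the outcome by telephone, and the site labels conflict

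*Protocol article*

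**What the plan says.** **Allocation.** Under Sampling and data collection, one team member generates the sequence. Two other named researchers and "the research assistants will be responsible for enrolling and assigning participants". Phase 2 sampling & data collection gives recruitment to the same roles: "researchers and research assistants will randomly recruit women attending an antenatal care visit and their partners". On the mechanism it says: "To implement the randomization, a table with the generated randomization sequence will be used". Each participant who agrees is placed in the next row, which fixes the group. The sequence is computer-generated and balanced 1:1; no block size is given.

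**Outcome collection.** The knowledge, intention and satisfaction surveys are done by telephone after 3 months. "The research assistants under supervision of the researchers, will administer the telephonic survey". The satisfaction items go to the intervention group only.

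**Analysis.** Phase 2 data analysis reports an unadjusted relative risk from Poisson regression on correct answers over total questions, counting unattempted and don't-know answers as incorrect. It relies on randomization to balance the confounders.

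**Sites.** Under Study site, FF Ribeiro Clinic is in the central business district and serves an urban community, while "Kgabo CHC, is situated in a large settlement, Ga-Rankuwa, catering to a semi-rural community". The sample-size text under Phase 2 sampling & data collection has the participants "spread equally and randomly across the two sites (Kgabo CHC[urban site] and Ga-Rankuwa[rural site".

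**The concern.** Random allocation prevents selection only if the person deciding whether to approach and enrol a woman cannot know her group. Separating generation from enrolment, as the article does, is half of that protection. The other half is keeping the list from the person who assigns, and the mechanism described has no step that does so. If staff can anticipate the next row, the choice of whom to approach, or when, can depend on the arm.

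The second exposure comes at follow-up. The primary outcome, knowledge, is collected by conversation, and a prompt or a second try can turn a don't-know into a correct answer. A caller who knows the arm may do this unevenly without intending to.

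The site labels matter for a different reason. The urban and semi-rural columns of mock Tables 1, 2 and 3 are defined by them.

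**Working it through.** The plan gives no figure for concealment or masking. The check is therefore mainly a comparison of sections, with two small calculations for scale.

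**1. Who does what.**

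| Task | Role | Section |
|---|---|---|
| Generate sequence | One team member | Sampling and data collection |
| Recruit | Researchers and research assistants | Phase 2 sampling & data collection |
| Enrol and assign | Two other named researchers and the research assistants | Sampling and data collection |
| Administer the 3-month survey | Research assistants, supervised by the researchers | Phase 2 sampling & data collection |

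Generation is separate. Recruiting, enrolling and assigning share the same roles, and the research assistants also collect the outcome.

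**2. How foreseeable is the next allocation?** It depends on who can see the table, which the article does not say.
- If the assigner can read the table, 100% of next allocations are known.
- If the table is hidden but all past allocations are remembered, the share forced by earlier ones in 1:1 blocks of size 2m is 1/(m + 1). For blocks of 4 (m = 2) this is 1/3 = 33%. For blocks of 6 (m = 3) it is 1/4 = 25%. For one balanced run of 420 (m = 210) it is 1/211 = 0.5%. Simulation gave the same values. The block sizes are assumptions.

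Custody of the list is therefore what decides the matter.

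**3. When does the caller learn the arm?** Only intervention participants get the satisfaction items, so the caller must know the arm when that block is reached. The article lists the blocks as background, intention, knowledge, satisfaction. If they are asked in that order, those items need not disclose the arm before the knowledge answers are given. The article does not say whether the call sheet shows the group.

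**4. Could the analysis reveal or repair selection?** The knowledge survey is described only at 3 months, and the effect is unadjusted. Mock Table 1 compares demographic variables such as schooling, which would show part of any selection indirectly. It contains no knowledge score taken before allocation, so a difference in starting knowledge could not be seen or adjusted for.

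**5. Balance of arms by site.** With 210 per arm spread equally over two sites, the target is 210/2 = 105 per arm per site. Suppose one balanced 420-row list serves both sites, with 210 women at each. The number in the intervention arm at a site is then hypergeometric:
- variance = 210 × 0.5 × 0.5 × (420 − 210)/(420 − 1) = 26.3, so SD = 5.1;
- 95% range = 105 ± 1.96 × 5.1, about 95 to 115.

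One list does not guarantee 105, but the likely departure is small.

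**6. Site labels.**

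| | Study site | Phase 2 sampling & data collection |
|---|---|---|
| FF Ribeiro Clinic | Urban | Not listed |
| Kgabo CHC | Semi-rural | Urban |
| Ga-Rankuwa | Where Kgabo CHC lies | A separate, rural site |

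These cannot both be right.

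**The case against.** The strongest reply is that this is a condensed article and that custody of a randomization list is detail usually kept in the full protocol. The article separates generation from enrolment, and it takes a row only once a participant agrees. Nothing says that staff can see future rows. This stands as a limit on the claim: a reader might infer that the table is open and the next group visible before consent, and the text does not say so. It does not remove the point, because the article positively describes a mechanism in which the enrolling roles assign from the table, and that stated procedure should be changed.

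Three other stronger readings also go beyond the documents.
- *The person who enrolled a woman later marks her answers.* The article names a role, not individuals, and says that assistants administer the survey. Scoring is defined as correct answers over total questions.
- *The caller knows the arm throughout.* The satisfaction items are listed last, so disclosure is certain only when they are reached.
- *Both problems favour the videos.* Staff could steer better-informed women to the videos, or those thought to need them most. The second would lower the video arm's scores.

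It can also be said that one list balances the sites well enough. That largely stands: an SD of about 5 around 105 is minor. The site labels may be an editorial slip, since Study site, Study population and Ethical considerations all name FF Ribeiro Clinic and Kgabo CHC. It still needs correcting, and it lends no weight to the other points.

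**Conclusion.** The point holds as a weakness in a stated procedure. The roles that recruit and enrol also assign from a sequence table with no described safeguard, so allocation may be foreseeable. The research assistants also collect the outcome in a call whose last-listed block discloses the arm. The unadjusted analysis, with no pre-allocation knowledge score described, could not detect or correct selection on knowledge.

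Neither the direction nor the size of any bias can be derived from the article. Any figure would rest on an assumed amount of steering or prompting, so none is given. The conclusion assumes that the full protocol adds no concealment or masking; if it does, the article should say so. Site balance is a minor matter. The contradiction in site labels is certain and rests on no assumption.

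**What to change.** For the remaining enrolments:

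1. The sequence generator keeps the list and releases each allocation, by message or numbered sealed opaque envelope, only after consent and background data are recorded.
2. Use one blocked list per site, so that arms are balanced by site as promised. Keep the block sizes from enrolling staff, since known short blocks would make a quarter to a third of allocations certain.
3. Keep the group off the call sheet. Where existing staffing allows, the caller should not be the person who enrolled the woman. Open the satisfaction block only after the knowledge and intention answers are saved.
4. Reconcile the site names and urban/semi-rural labels between Study site and Phase 2 sampling & data collection, then check mock Tables 1 to 3 against them.

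The registration data set reports 29 enrolled and recruitment suspended, without saying in which phase. If all 29 are trial participants, 420 − 29 = 391 allocations can still be protected. The plan should then state how those 29 sit alongside the new lists.

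The cost is a message or envelope per enrolment, a second list and a short delay at enrolment. The background questions, now listed within the survey given at 3 months, would be asked at enrolment. Changing callers depends on how assistants are deployed, which the article does not state.

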#### Phase 1 sampling & data collection

During Phase 1, purposive sampling will be used to select women and their partners attending antenatal care visits at the study sites for in-depth interviews. Health workers will be purposively selected based on their designated positions. Selected health workers could include community health workers, maternal-child health decision makers or experts, CHC managers, maternity and neonatal unit managers and sub-district or district managers of maternal, neonatal and child health programs. Only participants who provide informed consent to participate in the first phase of the study will be interviewed. The interview guide used during Phase 1 is presented in Additional file 1: Annexure 1.

In-depth interviews will be conducted with 10-15 pregnant women, who present for an antenatal care visit at the study sites. Additionally, in-depth interviews will be conducted with 10-15 health workers at the study sites. A semi-structured questionnaire will be used to guide the qualitative interviews of Phase 1.

The researchers will recruit expectant mothers and their partners after they present at the study sites for an antenatal care visit and will explain the purpose of the study. Expectant mothers who show an interest in participating in the qualitative study will be screened to assess if they meet the inclusion criteria. Informed consent will then be obtained from eligible expectant mothers and their partners. Researchers and research assistants will conduct the interviews in a private area at the respective study sites. All participants will receive ZAR 100 to compensate them for their time and expenses incurred by participating in our study.

#### Phase 2 sampling & data collection

During Phase 2 of the study, the randomized control trial, researchers and research assistants will randomly recruit women attending an antenatal care visit and their partners, inviting them to participate in the randomized control trial. Every participant will be required to provide informed consent before they can be included in the sample. Participants will be randomized into either the intervention group or the control group until the sample size of 420 has been reached. To implement the randomization, a table with the generated randomization sequence will be used, and as a participant agrees to participate in the study, they will be sequentially allocated to a row in the table that will determining the group that the participant will form part of. The sample size for the randomized control trial, was determined using the primary outcome of the study, change in knowledge. We will allocate participants equally to the treatment and control groups, through a balanced computer-generated random sequence. We use a 0.05 level of significance (*P* < 0.05) and a power of 0.9 with a two tailed test for significance.

Our hypothesis is that at the 3-month follow-up, participants in the control group will score 43% on the intention to change behavior score (12 points out of 28 points in the survey). We propose that after the 3-month follow-up the intervention group will score 61% (17 out of 28 points). This is an 18% absolute increase and a 1.41 times relative increase. A sample size of *n* = 140 was calculated for the intervention group and the control group. We then used an increase of 50% to account for potential participant drop-outs, bringing the sample size for the intervention group to *n* = 210 and the sample size for the control group to n = 210, spread equally and randomly across the two sites (Kgabo CHC[urban site] and Ga-Rankuwa[rural site]). Thus, a total of *n* = 420 participants for the entire randomized control trial will be required. These sample size calculations were carried out on G-Power 3.1.9.6.

Sample size calculations were based on the difference between two independent proportions using a z-test (Power: 0.9, Alpha 0.05, Allocation N1/N2: 1, p1 = 0.43, p2 = 0.61). The sample size per group was rounded up to the nearest 10 patients (N1 = 140, N2 = 140).

Expectant mothers assigned to the intervention group will watch the 10 Amandla Mama videos and their partners will receive the same 10 Amandla Mama videos via the social media platform, WhatsApp or short messaging service (SMS). The expectant mothers will be asked to provide the researchers with their contact details and the contact details of their partners. Partners who agree to participate in the study and who provide informed consent will receive the Amandla Mama videos by SMS or WhatsApp. The control group will receive existing treatment as usual-antenatal care only.

After 3 months, knowledge, behavioral intent, and user satisfaction surveys will be administered telephonically to all participants. The follow-up is conducted after 3 months to test long-term retention providing a better predictor for ongoing change. The research assistants under supervision of the researchers, will administer the telephonic survey. Data collected from participants who discontinue with or deviate from the study will not be used.

Surveys for the expectant mothers consist of a total of 61 questions: 10 background questions, 15 behavioral intention questions, 30 knowledge questions and 8 user satisfaction questions (refer to Additional file 1: Annexure 2). Surveys for partners consist of a total of 63 questions: 8 background questions, 18 behavioral intention questions, 30 knowledge questions and 8 user satisfaction questions (refer to Additional file 1: Annexure 3). The user-satisfaction questions, which consider how satisfied the participants are with the Amandla Mama videos, will only be administered to participants in the intervention group. All Phase 2 study participants will receive ZAR 100 to compensate them their time and expenses incurred by participating in our study.

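### The protocol contradicts itself on whether the mother or each individual participant is randomised and counted, and the single knowledge row makes no provision for couples

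*Protocol article*

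**What the plan says.** All quotes are from the protocol article, section Phase 2 sampling & data collection.

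- **Who is recruited.** Staff will "randomly recruit women attending an antenatal care visit and their partners, inviting them to participate in the randomized control trial". The Methods overview below Fig. 1 likewise describes the trial's participants as both groups, mothers and partners.
- **Who takes a row.** "as a participant agrees to participate in the study, they will be sequentially allocated to a row in the table".
- **Who is counted.** "Participants will be randomized into either the intervention group or the control group until the sample size of 420 has been reached".
- **Who was sized.** The calculation is a z-test for two independent proportions, and its unit is the patient: "The sample size per group was rounded up to the nearest 10 patients (N1 = 140, N2 = 140").
- **Who is assigned when the videos are delivered.** "Expectant mothers assigned to the intervention group will watch the 10 Amandla Mama videos and their partners will receive the same 10 Amandla Mama videos".

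Study population states that mothers without a partner remain eligible, so the share of participants who belong to a couple is unknown. Both surveys contain 30 knowledge questions. In Phase 2 data analysis, mock Table 3 has separate mother and partner rows for behavioural intentions but one Knowledge Score row. The effect measure is an unadjusted relative risk from Poisson regression, and no couple term is mentioned.

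**The concern.** Two things are at stake.

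The first is allocation. If each consenting person takes the next row, a mother and her partner can land in different arms. A control mother then lives with someone who holds the videos on his phone, which dilutes the contrast the trial is meant to measure. This cannot be repaired after enrolment.

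The second is precision. A couple shares one intervention and probably much of its knowledge. If both members enter one knowledge estimate as if unrelated, the standard error is too small. If partners also use up places in the planned 140 per arm, the trial carries less information than the calculation assumes.

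**Working it through.** **1. The two allocation rules side by side.** Under the row-per-participant rule with 1:1 allocation, the chance that two members of a couple fall in different arms is about 1/2. The chance that the mother is in control and her partner in intervention is about 1/2 × 1/2 = 1/4. Under the delivery rule both chances are zero, because the partner follows the mother.

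**2. The plan's own sample size.** Inputs from the protocol: p1 = 0.43, p2 = 0.61, two-tailed alpha 0.05, power 0.90, 1:1. The mean proportion is 0.52.

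- A = √(2 × 0.52 × 0.48) = 0.7065
- B = √(0.43 × 0.57 + 0.61 × 0.39) = 0.6950
- n = (z_alpha × A + z_power × B)² / 0.18²
- Two-sided: (1.960 × 0.7065 + 1.282 × 0.6950)² / 0.0324 = 159.8, so 160 per group
- One-sided: (1.645 × 0.7065 + 1.282 × 0.6950)² / 0.0324 = 130.1, so 131, which rounds up to 140

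The stated 140 is therefore not reproduced by the stated two-tailed test. Two-sided power at n per arm is Φ[(0.18√n − 1.960 × A)/B]. At n = 140 it is Φ[(2.130 − 1.385)/0.695] = Φ(1.072) = 85.8%. This shortfall exists under full independence and has nothing to do with couples. It is, however, the right baseline for what follows. The later steps of the plan do reproduce: 140 × 1.5 = 210 per arm, and 2 × 210 = 420.

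**3. Error rate if couples are pooled without clustering.** The documents give no within-couple correlation (rho) and no share of participants in couples (f); both are assumed here. The design effect is DE = 1 + f × rho, and the actual two-sided error of a simple z-test is 2 × [1 − Φ(1.960/√DE)].

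| rho | f = 1: DE | f = 1: error | f = 0.5: DE | f = 0.5: error |
|---|---|---|---|---|
| 0.1 | 1.10 | 6.2% | 1.05 | 5.6% |
| 0.3 | 1.30 | 8.6% | 1.15 | 6.8% |
| 0.5 | 1.50 | 11.0% | 1.25 | 8.0% |

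With f = 1 the true standard error is √DE = 1.05, 1.14 and 1.22 times the naive one.

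**4. Power if partners are among the 140 evaluable per arm.** Effective n = 140/DE, put into the power formula of step 2; the baseline is 85.8%.

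| rho | f = 1: effective n | f = 1: power | f = 0.5: effective n | f = 0.5: power |
|---|---|---|---|---|
| 0.1 | 127.3 | 82.4% | 133.3 | 84.1% |
| 0.3 | 107.7 | 75.7% | 121.7 | 80.7% |
| 0.5 | 93.3 | 69.5% | 112.0 | 77.3% |

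**5. Power if 420 counts mothers only.** With 140 evaluable mothers per arm, each with an evaluable partner on top, a pooled analysis has 280/(1 + rho) effective people per arm. Power is 98.4%, 96.5% and 93.9% at rho 0.1, 0.3 and 0.5, and 85.8% at rho 1.0. It never falls below the mothers-only figure.

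**6. Extreme bound.** If all 420 were in couples and only mothers were read out, there would be 105 mothers per arm. After the loss implied by the plan (1 − 140/210 = one third), 70 would remain, with 56.9% power.

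**The case against.** Parts of the text point to the mother as the unit. The delivery paragraph assigns mothers, who then supply their partners' contact details. The Methods overview speaks of partners of recruited mothers, and the rounding sentence counts patients. On that sequence the partner joins a mother who is already assigned, and couples are never split. This shows what was probably intended, but it does not remove the rule that each consenting participant takes a row, in an article that includes partners among the participants.

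A reader might infer that the protocol does count partners in the 420 and does pool both members of a couple as independent. Neither is stated. The single Knowledge Score row may simply reflect that both surveys have 30 knowledge questions, whereas the intention items differ (15 for mothers, 18 for partners). User Satisfaction also has one row. Clustered standard errors may be set out in an analysis plan that is not shown. Pooling therefore has to be treated as a conditional reading.

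The z-test figures also treat the outcome as yes/no per person, whereas the planned outcome is a score. With an assumed score SD of 0.25 to 0.35 and the same 18-point difference, a two-sample normal calculation gives 99% to 86% power even at 70 per arm. This stands: the power figures describe the plan's own binary method and are pessimistic for a score. Likewise, the error rates above are for a z-test on persons and do not carry over exactly to the Poisson model.

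**Conclusion.** The contradiction over the unit of allocation and counting is established from the printed text and needs correcting whatever the size of any power loss: staff enrolling a couple cannot follow both rules.

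The rest is conditional. If knowledge is pooled across couples without clustering, the intervals are too narrow, however 420 is counted. The two-sided error is about 6% to 11% for rho 0.1 to 0.5 with everyone in couples, and less otherwise. Power is lost through pairing only if partners are among the 140 evaluable per arm; it then falls from 85.8% to 82–69% with everyone in couples, or to 84–77% with half in couples.

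A reader might conclude that the stated 90% power fails because of the couples, or that true power is 57%. The documents support neither. The step from 90% to 85.8% is a separate fault, since 140 fits only a one-sided calculation. The 57% needs every participant to be in a couple, partners to count, and mothers alone to be analysed, although mothers without partners are eligible.

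**What to change.** - Allocate one row of the table per mother, and state that her partner inherits her group.
- State whether 420 counts mothers only. If it includes partners, restate the power for the number of mothers expected, from a two-sided calculation.
- In mock Table 3, make mothers' knowledge the primary row and add a separate partner row, as is already done for intentions.
- Use couple-clustered standard errors for any estimate that pools the two.

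The cost is a change of wording and one extra table row. The stated power may become less favourable if 420 is kept as mothers plus partners.

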**Fig. 1 Fig1:**
[figure not shown]
Overview of the Amandla Mama Study Methodology

In Phase 1 the Amandla Mama videos will be iteratively developed through, (i) scripting, (ii) storyboard development, and (iii) refining the developed storyboards by incorporating formative qualitative feedback from expectant mothers, their partners, and health workers gathered through in-depth interviews.

During Phase 2 of the study, the Amandla Mama videos, developed in Phase 1, will be tested using a randomized control trial. Participants will be expectant mothers and their partners living in South Africa accessing routine perinatal healthcare services. The intervention group will watch the Amandla Mama Videos, and the control group will receive treatment as usual for antenatal care only. Treatment as usual antenatal care consists of standard maternity care, as outlined in the South African National Department of Health’s “*Guidelines for Maternity Care in South Africa*” [10]. Maternity care is offered free of charge in the South African public health sector and is integrated into primary healthcare [10]. A survey will be used to gauge whether the intervention results in knowledge change. The surveys, developed by the research team, have been designed to measure change in maternal knowledge, intended behavior, and, user satisfaction. These will be administered to patients 3 months after receiving the intervention. Surveys will also be conducted with partners of the recruited expectant mothers in the study, given the documented benefits to mothers having partners participate in accessing maternal health care services. The partner surveys will have the same content as those designed for the expectant mothers but will be adapted to be relevant to the partner. Knowledge will be the primary outcome and intended behavior change will be the secondary outcome of this randomized control trial.

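### The sample size is attributed to knowledge but worded on the intention score, treats mean scores as proportions of people, and does not give 140 per arm on its own inputs

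*Protocol article*

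**What the plan says.** All of this is in the protocol article.

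- Outcomes (Methods, text under Fig. 1): "Knowledge will be the primary outcome and intended behavior change will be the secondary outcome of this randomized control trial".
- Basis of the sample size (Phase 2 sampling & data collection): it "was determined using the primary outcome of the study, change in knowledge".
- Hypothesis, in the next paragraph: "participants in the control group will score 43% on the intention to change behavior score (12 points out of 28 points in the survey"), and "the intervention group will score 61% (17 out of 28 points"). The text adds: "This is an 18% absolute increase and a 1.41 times relative increase".
- Method: "Sample size calculations were based on the difference between two independent proportions using a z-test", with p1 = 0.43, p2 = 0.61, power 0.9, alpha 0.05 and 1:1 allocation. The test is described as two-tailed. The result is 140 per group after rounding up to the nearest 10, then 210 per group (420 in all) after adding 50% for drop-out.
- Survey content, same section: for mothers, "15 behavioral intention questions, 30 knowledge questions and 8 user satisfaction questions" plus 10 background questions, with a stated total of 61. For partners: 8 background, 18 intention, 30 knowledge and 8 satisfaction questions, with a stated total of 63.
- Analysis (Phase 2 data analysis): an unadjusted relative risk from Poisson regression, where the rate is correct answers over total questions.

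**The concern.** Three things in the sizing paragraph do not fit together.

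1. The outcome named as its basis (knowledge) is not the outcome in the hypothesis (intention).
2. The 28-point denominator does not match the number of intention items given anywhere in the article.
3. The two percentages are average scores, yet they are used as if 43% and 61% of participants had an event. Nothing in the article turns a score into a success or failure for each person.

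At stake is whether the stated 90% power applies to the comparison that the trial will make. If it does not, the article gives readers no valid planning figure for the primary outcome. The rate in the primary analysis also has a denominator that is not settled.

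**Working it through.** **Which score has 28 points?**

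| Set | Items in text | Rows in mock Table 2 |
|---|---|---|
| Intention, mothers | 15 | 15 |
| Intention, partners | 18 | 18 |
| Knowledge | 30 | 28 |

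With one point per item, 17 points is impossible on the mothers' 15 intention items. Mothers' total: 10 + 15 + 30 + 8 = 63, but 10 + 15 + 28 + 8 = 61, the stated figure. Partners' total: 8 + 18 + 30 + 8 = 64 and 8 + 18 + 28 + 8 = 62; the stated 63 fits neither. Two of three clues therefore point to a 28-item knowledge score, and the third is silent.

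**Reproducing 140.** The pooled z-test formula is

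n = [z(α)·√(2·p̄·(1−p̄)) + z(power)·√(p1(1−p1) + p2(1−p2))]² / (p2−p1)²

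with p̄ = 0.52, √(2 × 0.52 × 0.48) = 0.7065, √(0.2451 + 0.2379) = 0.6950 and (0.18)² = 0.0324.

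- Two-sided 0.05, power 0.90: (1.960 × 0.7065 + 1.2816 × 0.6950)² / 0.0324 = 159.8, so **160** per arm. With unpooled variance it is 157, with continuity correction 171, and with the exact fractions 12/28 and 17/28 it is 163.
- One-sided 0.05, power 0.90: 131, which rounds up to 140.
- Two-sided 0.05, power 0.85: 137, which also rounds up to 140.
- Two-sided power at 140 per arm: (0.18 × √140 − 1.960 × 0.7065) / 0.6950 = 1.07, so power is **0.858**.

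The stated inputs thus do not give 140. The document does not show which setting did.

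**What the proportion formula assumes about the score.** Its SD is √(0.43 × 0.57) = 0.495, or 13.9 of 28 points. A score can have that SD only if everyone gets 0 or 28. The largest possible SD is √(12 × 16) = 13.9 at mean 12 and √(17 × 11) = 13.7 at mean 17.

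**The same difference as mean scores.** The document gives no SD, so the values below are assumptions. n per arm = 2 × (3.2415 × SD / 0.18)², two-sided 0.05, power 0.90.

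| SD (percentage points) | n per arm for 18 points | Detectable at 140 per arm | In items of 28 |
|---|---|---|---|
| 15 | 14.6 (15) | 5.8 points | 1.6 |
| 20 | 25.9 (26) | 7.7 points | 2.2 |
| 25 | 40.5 (41) | 9.7 points | 2.7 |

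The detectable difference comes from 3.2415 × √(2/140) = 0.387 SD. For a 5-point difference, 140 per arm suffices at any SD up to 5 / 0.387 = 12.9 points of 28.

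**Pairs.** The 0.387 SD assumes 140 independent completers per arm. Partners of women in the video arm receive the videos too, so couples share an arm. If all 140 were complete couples with correlation ρ, the figure becomes 0.387 × √(1 + ρ), from 0.39 SD at ρ = 0 to 0.55 SD at ρ = 1. The article does not say whether partners count in the 420.

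**The case against.** The strongest defence is that this is a one-word slip. The paragraph says it was sized on knowledge, 28 matches the knowledge rows in mock Table 2, and the mothers' total works only with 28. On that reading the article does state a target knowledge difference: 5 of 28 points. This largely stands. A reader might infer that the trial was sized on its secondary outcome, or that no detectable knowledge difference was ever set; the document does not support either as fact. The slip is not proven, however. The text says 30 knowledge questions for both groups, and the partners' total fits neither count. Multi-point scoring of intention items cannot be ruled out because the survey annexures are not shown, though the correct-over-total definition suggests one point per question.

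A second defence is that the proportion formula overstates the variance, so the error is on the safe side. That also stands. A reader might infer from the wrong formula, or from 160 against 140, that the trial is too small. For a comparison of mean scores it would be so only if the SD were above 12.9 of 28 points, close to the maximum possible. Nor does it follow that a null or small effect could not be interpreted, since the article commits to 95% confidence intervals.

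What the defence does not reach is the mismatch between calculation and analysis, which holds for either score, and the failure of the stated inputs to give 140.

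**Conclusion.** The point holds as a set of contradictions in the sizing paragraph, not as a finding of inadequate size.

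- The named outcome and the hypothesis disagree. A mislabelled knowledge score is the likeliest explanation.
- The knowledge item count is 28 or 30 depending on where one looks, and it is the denominator of the primary rate.
- The 90% power belongs to a comparison of proportions of people that the article neither defines nor plans to analyse. The direction of that error is conservative.
- Taken at face value, the calculation needs 160 per arm, and 140 completers give about 86% two-sided power. With 210 enrolled per arm, 160 completers remain if loss is at most 50/210 = 24%, against the 70/210 = 33% that the plan allows for.

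The item counts and the 160 and 86% figures follow from the document alone. The 15 to 41 per arm and the 5.8 to 9.7 points rest on assumed SDs of 15 to 25 percentage points and on independent participants.

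**What to change.** Keep 420 and rewrite the paragraph.

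1. Name the knowledge score as the basis, if that was meant, and reconcile its item count (28 or 30) across the hypothesis, the survey description and mock Table 2. Correct the survey totals at the same time.
2. Replace the two-proportion calculation with one for the participant-level knowledge score that is consistent with the planned analysis of correct answers over total questions, over a stated range of assumed SDs.
3. Restate the power or the detectable difference. Say whether mothers and partners both count in the 420, and allow for pairing if they do. The 0.39 SD at 140 completers per arm may be quoted only for independent participants.
4. If a binary endpoint was intended, define the pass mark, analyse it as binary, and give the power at 140 per arm as about 86% two-sided.

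The cost is one paragraph, an aligned item count and a short recalculation. No extra participants are needed.
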